## Results

The study was funded in 2021 with public funds from Conseil Régional d’Aquitaine and the Fondation International pour la Recherche Appliquée au Handicap (FIRAH), Klesia, and Comité National Coordination Action Handicap (CCAH).

Figure 3 shows the flowchart of the recruitment process. We initially recruited 37 eligible teams who were allocated to either the experimental or control group, which resulted in a sample size of 157 participants (2-7 people per team). At baseline, 31 individuals did not complete the questionnaires, leading to the exclusion of 11 teams due to incomplete data. In September 2023, the recruitment ended with 13 teams participating in the experimental condition (n=82) and 11 teams in the control condition (n=45). The experimental group is larger than the control group due to the nature of our action-research approach. Participants and partners expressed a strong preference for being included in the intervention to benefit from the CoEd app, viewing control group assignment negatively. To address this while maintaining rigorous assessment, we included more participants in the experimental group, ensuring sufficient data for analysis and respecting the ethical considerations of action research.

At the end of data collection (June 2024), a total of 59 individuals had dropped out: They stopped responding to the questionnaires and did not reply to our follow-up attempts. Consequently, there were 89 remaining participants at the 3-month follow-up and 67 participants at the 6-month follow-up. Data cleaning and analysis began in March 2025, and results are expected by June 2025. We anticipate that the findings may be ready for publication by the end of 2025, although this timeline remains provisional.

**Figure 3 figure3:**
[figure not shown]
Flowchart of participant recruitment.

## Discussion

### Expected Results and Comparison With Prior Work

This research protocol was developed to empirically evaluate the impact of a digital technology solution on collaborative relationships among stakeholders in inclusive education. Conducting a field study with a quasi-experimental protocol will provide true empirical support of the technology’s utility and effectiveness for fostering stakeholder collaboration. Through the targeted primary outcomes, we particularly expect an improvement in the quality of interpersonal relationships as well as more congruent cross-stakeholder attitudes toward school inclusion while empowering each stakeholder in their capabilities to achieve their own goals as educator and to support child in their IEP (RQ1). We also expect a beneficial effect of using the CoEd application on child-related outcomes (RQ2) and on the quality of life of stakeholders and children (RQ3).

Meyer et al [35] identified 6 digital projects and a strategy using an existing social network, all at different development stages. Of these projects, 3 used participatory design, 4 conducted needs analyses, and 3 were field-tested. However, none included a control group nor aimed to evaluate the impact on school inclusion, IEPs, stakeholder interactions, or health and well-being dimensions. From this review, it becomes evident that conducting quasi-experimental field studies and involving a substantial number of educational teams and various stakeholders will be an essential contribution. Building on this, our protocol seeks to provide robust evidence for a digital co-education tool designed with user-centered design methods and approaching a gold standard methodology.

### Strengths and Limitations

The CoEd application has already completed all the design and user testing in order to reach the step of empirical evidence thanks to this study (see [36] for the design study). Furthermore, our field study included evaluations that cover more broadly other critical indicators for co-educators, such as their mental health using the burden and quality of life assessments. There is strong evidence of the great influence of perceived self-efficacy on a person’s well-being [59,60]. Hence, we will be able to explore the links between the primary outcomes (interpersonal relationships, attitudes toward school inclusion, and self-efficacy) and some health measures. For the children, the collaboration benefits from technology could promote, by the bounds effect, their sense of school inclusion, school-life satisfaction, and overall well-being through an effect on parent-teacher relationships and collaboration between stakeholders [6,7,61-63]. This technology could also facilitate the implementation of IEPs by leveraging each stakeholder’s expertise [6,8] and, as a result, increasing the educational achievement (academic and social objectives) for each child.

Additionally, the log data from the CoEd application will provide insights on its actual usage across time and the targeted primary outcomes. For instance, RQs could address the traditional dilemma between quality and quantity of exchanged information, or content analyses could even document interpersonal tensions and their potential relation with a degraded partnership in the team and vice versa.

For the intervention group using the CoEd application, we are collecting data on usability, technology acceptance, and usage factors. This assessment is of great importance in studies examining the impacts of technology-based interventions, as usability and effectiveness are intrinsically related, and is part of most studies evaluating this kind of intervention [37].

These secondary indicators address the needs of project stakeholders (inclusive school policymakers, school organizations, teachers, practitioners, parents, and children with SEND) for successful participatory achievements and pave the way for innovative research, such as exploring relationships between CoEd acceptance and effectiveness in inclusive school environments. Most of the participants of this study are people who did not participate in the design steps of the project. Therefore, the bias from “being both designer and evaluator” is limited, and the results from this study will provide insight on the efficacy of using a citizen science approach in the domain of inclusive education. This study combines a traditional top-down approach (ie, expectations relative to specific primary criteria for a prescriptive purpose) with a bottom-up approach driven by the field expertise of the main stakeholders of school inclusion. As a reminder, the study outcomes have been cobuilt thanks to focus group methods involving actual stakeholders as well as researchers in the field (see Multimedia Appendix 2 for details about the focus group sessions). This citizen science approach (albeit risky) contributes to bridging science and practice, facilitating rapid societal impact, and emerging new research issues [64,65]. The results from this study could also contribute to documenting the effectiveness of citizen science and participatory design methods in designing innovative technologies tailored to the specific needs of people, especially in health and disability domains [24,65,66].

From our combined approaches, the study consortium encountered a few issues that reinforced the study-related challenges, especially with children with SEND and with a technology-based intervention. First, major challenges were related to the quasi-experimental study design in which the CoEd intervention condition is compared with a control condition where there are fewer teams. We paid great attention to matching the 2 groups with respect to the factors known for influencing the primary outcomes as well as possible. These factors include the size of the team, demographic factors, and the SEND of the child. Nonetheless, we are aware that such a matching method does not neutralize possible biases related to differences in the group size. We plan to explore the impact of any variable that is not matched between groups to investigate its impact on the intervention’s effect. A second study challenge was the great variability in the participants’ technological skills in the CoEd condition. Indeed, computer skills and prior experience with technology will necessarily influence the experience with using a digital tool and, in turn, modulate the intervention’s effects. We set up a standardized training phase for the use of CoEd application according to training use scenarios and provided both written and video tutorials to help people handle the CoEd application. In addition, the questionnaire on technological skills will be used as a covariable to explore the impact of this interindividual variability on the intervention’s effects. Another study challenge was associated with the increasing digitalization of schools, whether in teaching, student support, or parental involvement. Since the COVID-19 pandemic, this digitalization has significantly increased, especially in the field of education [67]. However, the extensive digitalization during the COVID-19 pandemic brought issues related to digital anxiety and data protection [68], increased screen time, and the effects on well-being and interpersonal relationships [69-71]. In this project, these themes were central during design and development steps, as it involved processing data concerning children with NDD. This point was addressed during the participatory design steps and proved to be a very important one for future users [36]. During the development steps, we made data security a priority, so that users can use the system with complete confidence (compliance with regulations, security certification). Finally, the last challenge our research had to confront was related to the context of digital development in France. The French government has introduced a new digital tool to bridge the gap between decision-making bodies for educational obligations and resources allocated for the implementation of an IEP and schools. This deployment has led teachers to increase digital data input on academic difficulties and IEP accommodations. However, this deployment has caused confusion with CoEd and could lead some teachers to limit their participation, as some data would need to be entered both in CoEd and the governmental digital tool. However, there are important differences between the CoEd application and the governmental tool: The latter is more oriented toward archiving aims and digitalization of the IEP, while the CoEd application promotes free sharing of experiential knowledge from each stakeholder, which indirectly contributes to IEP implementation and follow-up. In addition, the CoEd application allows stakeholders to communicate with each other about daily events, which is not covered by the governmental tool. In this context, the CoEd application can be viewed as an aid for following IEP objectives and to better support the use of the governmental app through complementary features.

Despite all these challenges, the outcomes of the CoEd study will yield significant insights on the benefits of a digital collaborative tool for teaching students with SEND. It will also yield some insights on the communication factors influencing the health of stakeholders and children. The study will also inform the feasibility of technology-based personalization of IEP and will likely teach some useful lessons for future technology-based field studies regarding empowering stakeholders to teach children with SEND.

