### Aims

We propose to conduct a field study aiming to evaluate the impact of using the CoEd web application on 3 outcomes. First, we hypothesized that the CoEd application will improve communication and relationships between stakeholders (family, school, and health care practitioners), as well as their attitudes toward school inclusion, and increase each stakeholder’s perceived self-efficacy (research question [RQ]1). Second, we hypothesized a beneficial effect of using CoEd on the child in terms of behavioral or academic functioning (RQ2). Third, we expect that using CoEd results in a better quality of life for both the stakeholders and the children (RQ3). Finally, as it is crucial when evaluating technology to verify that it is both effective and usable [37], we added measures related to the user experience of participants. Thanks to the participatory design, we expected that the CoEd application will elicit a good user experience (RQ4).

The paper follows the SPIRIT (Standard Protocol Items: Recommendations for Interventional Trials) guidelines for reporting study protocols [38]. The SPIRIT checklist for this paper is provided in Multimedia Appendix 1.

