### Eligibility Criteria

To participate, a support team had to consist of at least two stakeholders, including at least one of the parents. Additionally, the pupil had to be aged between 10 years and 16 years, enrolled in secondary school, be taught in mainstream settings, and have a diagnosis of ASD, attention-deficit/hyperactivity disorder, or intellectual disability (IQ<70). The pupil needed either an established diagnosis or to be undergoing a multidisciplinary intervention for diagnosis.

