### Outcome Measures

#### Selection of Outcome Measures

Outcome measures were chosen from the researchers’ hypotheses and participatory decision-making. In 2 focus groups, parents, teachers, and health care professionals discussed the CoEd application’s potential impact and evaluation criteria (Multimedia Appendix 2). Participants reviewed preselected indicators and suggested new measures, especially concerning quality of life and caregiver burden, for the field study. As a result, the primary outcomes include 3 main dimensions (ie, stakeholders’ relationships, perceived individual efficacy, and attitudes toward school inclusion). To this end, parents, teachers, and health care professionals completed a series of common or specific questionnaires (Table 1). The secondary outcomes include measures for stakeholders (burden and quality of life) and for the children (quality of life, school well-being, and school inclusion perception; Table 1). Additionally, a measurement of technology experience that covers technology skills and CoEd experience was included for the intervention group (Table 1). Although some questionnaires had a validated French version, others did not. In the latter case, as we are French native speakers, we translated them in collaboration with native English speakers. The scales used are presented in Table 1.

**Table 1 table1:** Description of the assessment batteries to address the targeted (primary and secondary) outcomes and technology experience of participants.

Outcomes, dimension, and subdimension				Questionnaire		Respondent						
						Child		Parent		Teacher		Professionals

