#### Planned Statistical Analyses

We plan to conduct pre-post mean comparison analysis on primary (RQ1) and secondary outcomes (RQ2 and RQ3) to assess within and between-team effects of the intervention. We will conduct within-team analyses using 1-way ANCOVA to compare pre and postintervention differences separately for each team’s experimental and control groups. This approach helps identify specific changes within teams and assesses differential effects between groups. Additionally, a between-team analysis will treat all participants as a single population, using repeated-measures ANCOVAs or linear regression analyses to examine the overall intervention effect across teams. This global analysis disregards team distinctions to assess the intervention’s overall impact. In addition, using ANCOVA will allow us to control for potential bias coming from the variability in technological skills (Computer Usage Questionnaire; see Table 1) as well as any variable that may compromise the homogeneity across groups. Missing data will result in the exclusion of related observations, and dropouts will be monitored to explore the reasons.

By combining these methods, we aim to provide a comprehensive evaluation of the psychological intervention’s effectiveness, considering both within-team variation and overall effects.

To assess the user experience (RQ4), only the participants of the CoEd intervention condition answered the user experience questionnaire. These data will be analyzed through descriptive statistics and compared with questionnaire-related benchmarks.

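### Designer-evaluator bias is called limited without a count, and the RQ4 benchmark comparison does not separate co-designers from the other CoEd raters

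*Protocol article*

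**What the plan says.** Under Strengths and Limitations the article says that "Most of the participants of this study are people who did not participate in the design steps of the project", and infers from this that "the bias from “being both designer and evaluator” is limited". It gives no number, arm or role for the people who did take part in the design, and it goes on to say that the results will inform the value of the citizen science approach.

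The Eligibility Criteria concern team composition and the pupil: "To participate, a support team had to consist of at least two stakeholders, including at least one of the parents", followed by age, schooling and diagnosis. Earlier involvement in designing CoEd is not mentioned. It is also absent from the matching factors in the Discussion, which are team size, demographics and the child's needs.

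For RQ4, Planned Statistical Analyses says that only the CoEd arm answers the user-experience questionnaire, and that "These data will be analyzed through descriptive statistics and compared with questionnaire-related benchmarks". The Aims section attributes the expected good user experience to the participatory design.

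On outcome selection, the article reports: "In 2 focus groups, parents, teachers, and health care professionals discussed the CoEd application’s potential impact and evaluation criteria". It does not say whether any of these people later enrolled.

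Two general provisions exist. The ANCOVA may adjust for variables that make the groups unlike, and the Discussion promises to explore variables that are not matched between groups. Neither names design involvement.

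**The concern.** The article recognises a bias and then sets it aside on the strength of one unquantified word. Whether the bias is small depends on how many co-designers there are, which arm they are in, and how differently they score. None of these is given.

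RQ4 is where this matters most. The outcome is a subjective rating of the app, only app users give it, and the comparator is a benchmark for other digital products. A co-designer's favourable rating goes straight into the mean, and nothing in the design reveals it. The hypothesis makes this worse. If the claim is that participatory design yields a product that users like, people who took part in that design are the least informative raters. A good RQ4 score would then be read as support for the participatory method, when part of it could be goodwill from those who helped to make the app.

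For RQ1 to RQ3 there is a control arm and a baseline, so the concern is conditional: it needs co-designers to be concentrated in one arm.

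**Working it through.** The plan states no figure on this point, so there is nothing to reproduce. The shares and shifts below are assumptions. The participant counts come from the article's Results section, and d = 0.600 comes from its Power section.

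**1. What the word *most* allows.** It describes the participants of the whole study. Taking the 127 allocated after baseline, the largest whole number below half is 63. Nothing says how they divide between arms. If all 63 were in the CoEd arm they would be 63/82 = 77% of it; at the other end, the number could be very small. The word therefore does not cap the share among CoEd raters at one half. The raters are also likely to be fewer than 82, since 89 of the 127 remained at 3 months and 67 at 6 months, with no split by arm given.

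**2. RQ4.** Shift in the mean score = *p* × *s*, where *p* is the share of co-designers among raters and *s* is how much higher they score on the User Experience Questionnaire (-3 to +3).

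| *p* | *s* = 0.5 | *s* = 1.0 |
|---|---|---|
| 10% | 0.10 × 0.5 = 0.05 | 0.10 × 1.0 = 0.10 |
| 40% | 0.40 × 0.5 = 0.20 | 0.40 × 1.0 = 0.40 |

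The article gives no benchmark thresholds, so whether such a shift would change the benchmark category cannot be said.

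**3. Do the general provisions reach RQ4?** Both deal with imbalance between the two groups. RQ4 uses one group, so neither applies.

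**4. RQ1 to RQ3.** Bias in SD units = (*p* in CoEd arm − *p* in control arm) × *b*, where *b* is the shift in a co-designer's result. With equal shares and the same shift in both arms, this is zero. For the least favourable split, put all co-designers in the CoEd arm. With 82 against 45 independent people, the standard error is √(1/82 + 1/45) = 0.186 SD. With no true effect, a two-sided 5% test (level assumed) rejects with probability 1 − Φ(1.96 − bias/0.186) + Φ(−1.96 − bias/0.186).

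| Share in CoEd arm | *b* (SD) | Bias (SD) | Bias / 0.600 | Rejection rate |
|---|---|---|---|---|
| 10% | 0.5 | 0.05 | 8% | 5.8% |
| 20% | 0.5 | 0.10 | 17% | 8.4% |
| 20% | 1.0 | 0.20 | 33% | 19% |
| 49% | 0.5 | 0.245 | 41% | 26% |

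Team clustering is ignored. A small minority does little harm and a large one could do a good deal. The article's wording does not distinguish the two.

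**The case against.** The strongest reply is that the authors name this bias themselves, that RQ4 is only descriptive and is complemented by objective log data on app openings and posts, and that a count by arm or a sensitivity analysis is detail an article may leave to a fuller document. Part of this stands. Log data are a useful complement, and silence alone would not be a finding. But the article is not silent: it draws a conclusion about the size of the bias, and it fixes an RQ4 comparison that does not set co-designers apart. The log data measure use, and they do not correct the questionnaire scores that are compared with the benchmarks.

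Several stronger readings are tempting, and the article does not support them.

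- A reader might infer that trial participants chose the outcomes by which the app is judged, because the article writes "Participants reviewed preselected indicators and suggested new measures". In that sentence the participants are focus-group members. The later statement that "the study outcomes have been cobuilt thanks to focus group methods involving actual stakeholders as well as researchers in the field" also speaks of stakeholders, not of enrolled people.
- A reader might infer that co-designers had no true pre-exposure baseline. The Procedure section says that child pages and logins were created on assignment to CoEd, and that manuals and tutorials followed the baseline measures. Helping with design is not the same as using the app for one's own pupil. For the same reason, a co-designer in the control arm who knows the app has not thereby received the intervention.
- A reader might infer that RQ1 to RQ3 are biased. Non-random allocation, recruitment through project partners' networks and a strong preference for CoEd make an uneven split plausible, but no passage shows one. Those outcomes are not ratings of the app, and the provisions for unbalanced variables could cover design involvement if it were recorded.
- A reader might infer that co-designers were kept because they are few. The article uses the word only to comment on the size of the bias.

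**Conclusion.** The point holds in a limited form. The article implies that an unquantified minority of participants helped design CoEd, and its claim that the resulting bias is limited has no support beyond the word *most*. The consequence is clearest for RQ4, which has no comparison arm and which tests a hypothesis about participatory design partly on ratings from those who took part in it. For RQ1 to RQ3 the risk is conditional on an uneven split between arms, and the documents do not establish one.

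The size is illustrative only: 0.05 to 0.40 points on the User Experience Questionnaire under the assumed shares and shifts, and anything from no bias upwards for RQ1 to RQ3. The conclusion rests on the ordinary reading that, if most did not take part, some did. If the count proves to be very small, reporting it would give the authors' statement the support it now lacks.

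**What to change.** 1. Flag each participant who took part in the design steps, and report the number by arm. That the authors can say *most* suggests that they can identify these people.
2. Make the main RQ4 benchmark comparison in CoEd participants without design involvement, and report co-designers separately beside it. Settle this before scores are examined by flag.
3. Repeat the RQ1 to RQ3 group comparison without flagged participants in either arm, as a sensitivity analysis.
4. Under Strengths and Limitations, replace the statement that the bias is limited with the counts by arm and the results of steps 2 and 3.

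The cost is one indicator variable, a change to the analysis text, and somewhat fewer ratings in the main RQ4 summary. No change to eligibility or to the outcome questionnaires is needed. The article does not describe how trial identification numbers link to design-phase records; if no link was kept, participants would have to be asked.

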**Methods:**

This protocol describes a longitudinal, nonrandomized controlled trial, with baseline, 3 month, and 6-month follow-up assessments. The intervention consisted of using the web-based CoEd application for 3 months to 6 months. This application is composed of a child’s file in which stakeholders of the support team can share information about the child’s profile, skills, aids and adaptations, and daily events. The control group is asked to function as usual to support the child in inclusive settings. To be eligible, a support team must be composed of at least two stakeholders, including at least one of the parents. Additionally, the pupil had to be aged between 10 years and 16 years, enrolled in secondary school, be taught in mainstream settings, and have an established or ongoing diagnosis of autism spectrum disorder, attention-deficit/hyperactivity disorder, or intellectual disability (IQ<70). Primary outcome measures cover stakeholders’ relationships, self-efficacy, and attitudes toward inclusive education, while secondary outcome measures are related to stakeholders’ burden and quality of life, as well as children’s school well-being and quality of life. We plan to analyze data using ANCOVA to investigate pre-post and group effects, with a technological skills questionnaire as the covariate.

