	**CoEd** **application experience**											
		Subjective user experience	User Experience Questionnaire, short version and Technology-based Experience of Need Satisfaction (TENS)^a^		—		X		X		X	
		Objective user experience	The uses and usages of the CoEd application are quantified with the following indicators across periods of 3 months or 6 months: (1) number of times the application is opened and (2) number of exchanged posts		—		X		X		X	

^a^Translated in French by the authors.

^b^Not applicable.

^c^Intervention group only.

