##### Measurement of Technology Experience (Experimental Group Only)

To assess the potential effect of prior technology skills on the use of CoEd, parents and professionals completed the Computer Usage Questionnaire [56] that consists of a self-reported measure of 18 questions asking for the frequency (5-point scale ranging from never to very often) of different computer activities and software usage.

To address the specific user experience with the CoEd application, the User Experience Questionnaire short form [57] was selected as the measurement. It uses a 7-point Likert scale (–3=fully agree with negative term to +3=fully agree with positive term) of subjective perceptions of users in terms of both the hedonic and pragmatic dimensions toward a given product and according to a benchmark for digital products. The Technology-based Experience of Need Satisfaction-Interface [58] is related to the self-determination theory framework for assessment and uses a 5-point Likert scale (1=Do Not Agree to 5=Strongly Agree) to assess basic psychological need (autonomy, competence, relatedness) satisfaction through the interaction with the interface or system. Satisfaction of these needs is arguably associated with sustained engagement with a technology.

Complementary to the subjective measures, direct measures of CoEd use and usage are collected through active interactions (log data) with this web application, in particular the number of times the app was opened and the number of exchanged posts (Table 1).

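### A technology-skills covariate, collected in the CoEd group only, cannot show whether the intervention's effect varies with skill

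*Protocol article*

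**What the plan says.** The article gives the Computer Usage Questionnaire two roles.

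- **Adjustment.** The Abstract (Methods) announces ANCOVA "with a technological skills questionnaire as the covariate". Planned Statistical Analyses says that "using ANCOVA will allow us to control for potential bias coming from the variability in technological skills". The between-team analysis is described as "using repeated-measures ANCOVAs or linear regression analyses to examine the overall intervention effect across teams".
- **Modulation.** Strengths and Limitations names variability in skills as a study challenge, because "computer skills and prior experience with technology will necessarily influence the experience with using a digital tool and, in turn, modulate the intervention’s effects". Its answer is that "the questionnaire on technological skills will be used as a covariable to explore the impact of this interindividual variability on the intervention’s effects". The same section also promises to look at how any unmatched variable affects the intervention's effect.

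No group-by-skills term, moderation model or skill subgroup is named anywhere in the article. The footnote to the technology-experience block of Table 1, which contains this questionnaire, reads "Intervention group only". The heading of the subsection describing the questionnaire and the text under Selection of Outcome Measures say the same.

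**The concern.** Asking whether skills modulate the effect of CoEd means asking whether the CoEd-minus-control difference changes with skill. A covariate main effect asks whether skill predicts the outcome, while holding the group difference constant over skill. The article therefore names a tool that assumes away the variation it says must occur.

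The stake is what is concluded about who benefits. A significant covariate could be reported as showing that skilled users gain more from CoEd when skilled adults simply have better outcomes in either arm. A null covariate could be reported as no modulation when the slopes differ between arms. Either reading could misdirect decisions on training and support.

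**Working it through.** The plan gives no figure to reproduce here, because the question is one of model form.

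**1. What each model estimates.** Let s be the standardised skill score and let the outcome be a post score or a pre-post change.

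- Control: mean = a + c·s
- CoEd: mean = a + τ + (c + m)·s
- Effect of CoEd at skill s: τ + m·s

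Modulation is m. With the same skill distribution in both arms and a share w of participants in CoEd, the additive ANCOVA returns a single group effect τ and a pooled slope c + w·m. Only the group-by-skills term returns m. A slope fitted in CoEd users alone returns c + m.

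**2. Numbers.** The group sizes are those in the Results section, 82 and 45, so w = 82/127 = 0.646. The other inputs are assumptions: τ = 0.6 (taken from the effect size under Power), residual SD 1, independent participants, two-sided 5%, 3,000 runs, and skill observed in both arms.

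| Slopes: control, CoEd | Pooled slope c + w·m: formula / simulated | Covariate significant | Group-by-skills significant | CoEd-only slope significant |
|---|---|---|---|---|
| 0.40, 0.40 (m = 0) | 0.40 / 0.401 | 99.1% | 4.5% | 93.7% |
| 0, 0.40 (m = 0.4) | 0.646 × 0.4 = 0.258 / 0.257 | 79.8% | 56.9% | 93.4% |
| −0.258, 0.142 (m = 0.4) | 0 / 0.001 | 4.8% | 54.9% | 24.2% |
| 0, 0 | 0 / 0.000 | 5.3% | 4.9% | 4.5% |

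The additive group effect was about 0.60 in every row (0.598 to 0.608), whether or not the true effect varied with skill. Rows 1 and 2 give a significant covariate and the same CoEd-only slope of 0.40, yet only row 2 contains modulation.

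**3. What pre-post change removes.** If skill shifts the level by the same amount b before and after, then change = (post + b·s) − (pre + b·s), and b cancels. This was checked with 57 CoEd participants, an assumed within-person correlation of 0.6, no modulation and 4,000 runs. At skill correlations of 0.2, 0.3 and 0.4, the slope on the post score rejected in 33%, 65% and 89% of runs. The slope on change rejected in 5.2%, 5.0% and 5.7%, which is nominal. A stable level effect is therefore not mistaken for modulation in a change analysis. The slope that remains among CoEd users is c + m, where c is now skill-related change that would have occurred anyway. Separating c from m needs controls with skill scores.

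**4. Whether the interaction can be fitted.** Planned Statistical Analyses excludes observations with missing data. If only CoEd participants have a skill score, every complete case has group = 1. The group column then equals the intercept and the group-by-skill column equals the skill column. The design matrices [1, group, skill] and [1, group, skill, group×skill] both have rank 2, so m is not estimable, and in such a model neither is τ.

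**5. Precision if control skill data do exist.** The SE of the interaction is about √(1/82 + 1/45) = 0.186 SD per SD of skill. The 95% interval is therefore about ±1.96 × 0.186 = ±0.36, and power for m = 0.4 is Φ(0.4/0.186 − 1.96) ≈ 58%. Both ignore team clustering and dropout.

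**The case against.** - **Interaction terms belong to the analysis plan, and repeated-measures ANCOVA can carry time-by-covariate terms.** It is true that the article lists no model terms and does not exclude interactions. But it is not silent either: it names the covariate as the tool and says what it will show. A time-by-skills term shows only that change varies with skill. Modulation needs group-by-time-by-skills, which requires skill scores in controls.
- **The planned analysis is pre-post.** This stands and limits the point. A reader might infer that a significant skills slope among CoEd users shows only that skilled adults score differently. For change scores that does not follow, as step 3 shows, and the 33%, 65% and 89% apply only to a post-score analysis.
- **Missed modulation depends on the slopes.** This also stands. A reader might infer that the covariate usually misses real modulation. With slopes of +0.3 in CoEd and −0.3 in controls (57 versus 32), it detects 14% against 78% for the interaction. Nothing in the article suggests that skill worsens outcomes in controls. With slopes of 0 and 0.4 at the same sizes, the covariate rejects in 68% of runs and the interaction in 46%. The covariate reacts there, but cannot say why. The 57/32 split is itself an assumption.
- **Unmatched variables.** The remark on these follows a discussion of matching and bias, where covariate adjustment is a standard tool. It needs changing only where a statement about effect modification is really meant.
- **It is exploratory.** Agreed. Skill modulation is not among the four research questions.

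**Conclusion.** The concern holds as a mismatch between tool and purpose. A covariate main effect cannot show that the effect of CoEd varies with skill. Because the questionnaire is collected in the intervention group only, the interaction that could show it is not estimable. What can be learned is whether change among CoEd users is associated with skill, without knowing how much of that association would have arisen under usual practice.

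The algebra and the rank result do not depend on assumed values. The rank result rests on the article's statement that controls have no skill scores. The rejection rates are illustrative and rest on assumed slopes, SDs and independence.

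A reader might infer that covariate adjustment is wrong in itself, or that the primary and secondary comparisons fail on this account. This point supports neither. Adjustment is a legitimate aim where the covariate exists in both arms, and no research question depends on the modulation statement. The point is minor.

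**What to change.** In Planned Statistical Analyses and in Strengths and Limitations:

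1. Separate adjustment from modulation, and draw no conclusion about modulation from a covariate term.
2. Report the slope of pre-post change on skill as an exploratory association among CoEd users, and delete the statement that it shows an impact on the intervention's effects.
3. If control skill data do exist, fit group-by-skills (group-by-time-by-skills in the repeated-measures model), report it with its confidence interval and label it exploratory.
4. For unmatched variables measured in both arms, adjust for confounding. Add a group-by-variable term only where a statement about the variable's impact on the intervention's effect is intended.

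Items 1 and 2 change wording only and need no new data. Items 3 and 4 add model terms where the data allow. Data collection ended in June 2024, so baseline skill scores for controls cannot now be added if they were not taken. The price is a narrower claim and, where an interaction can be fitted, a wide interval.
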